### Ethics approval

The study protocol was approved by the University of Manitoba Human Research Ethics Board (reference number: H2012:182).

### Sample size calculation

In this pilot trial, a formal sample size calculation was not carried out. Thirty participants [31] will be recruited and allocated into two groups throughout the data collection period.

### Interventions

#### Control group

Based on previous studies [3,32-37], a conventional hand exercise program targeted to improve finger range of motion and hand strength has been compiled. The exercises of the conventional hand exercise program are: making a full fist by flexing the metacarpal phalangeal, proximal interphalangeal and distal interphalangeal joints of all fingers; making a small fist by flexing only the proximal and distal interphalangeal joints of all fingers; flexing and extending the wrist; touching the tip of each finger with the tip of the thumb; spreading the fingers as much as possible and closing them; raising the fingers as much as possible; hand intrinsic strengthening with 85 g medium-resistance therapeutic putty; and hand strengthening with a dumbbell.

#### Experimental group

The task-oriented training program is targeted to improve hand function during everyday tasks requiring dexterity functions and strength. Training with a few different objects with specific therapeutic values is listed below and is illustrated in Figure 3. The random manipulative movements described for each object task will be used to control the motion of the computer game cursor.

**Figure 3 F3:**
[figure not shown]
**Task**-**oriented training with a few selected objects.** (**A**) A bottle cap is manipulated by rotating it left or right. (**B**) A medium-sized ball is manipulated by rotating it left or right. (**C**) A flat wooden board is manipulated by tilting it up down and *vice versa*. (**D**) A dumbbell is used for strengthening the wrist extensors.

##### Therapeutic values: precision skill training

The following involve training of fine finger manipulations using small objects and precision grips. The manipulations are within the digits involving fine mobility in the joints moved.

1. Object selected: a door key

Method: the key is held between the pad of the thumb and the lateral side of the index finger and the task requires rotating the key to the left or right.

2. Object selected: a bottle cap

Method: the bottle cap is held between the pad of the thumb and the index or middle fingers and the task requires rotating the cap to the left or right (Figure 3A).

##### Therapeutic values: manual dexterity

The following involve training of gross finger hand manipulations with medium–large objects and power grasps. The manipulations involve use of the whole hand and the palm involving graded mobility at metacarpal phalangeal, proximal interphalangeal and distal interphalangeal and wrist joints.

3. Object selected: a sport ball (size of a tennis ball)

Method: the ball is held with the whole hand and the task requires rotating the ball to the left or right direction (Figure 3B).

4. Object selected: a plate or a lightweight flat wooden board

Method: the plate/board is held with the whole hand and the task requires tilting the plate/board up or down (Figure 3C).

5. Object selected: a drinking glass

Method: the glass is held with the whole hand and the task requires rotating the glass forward down or up straight.

##### Therapeutic values: strengthening

6. Object selected: half-filled jug

Method: the jug is held with the whole hand around the handle and the task requires tilting the jug sideways up or down, simulating pouring activity.

7. Object selected: a dumbbell

Method: a dumbbell held with the whole hand and forearm supinated or pronated can be used for graded strengthening of wrist flexors or extensors (Figure 3D).

### Outcome measures

#### Primary outcome measure

The primary outcome measure will be the Arthritis Hand Function Test, an 11-item performance-based test that measures grip and pinch strength, dexterity, applied strength and dexterity in people with arthritis. Test–retest reliability of the Arthritis Hand Function Test measured by the intraclass correlation coefficient in 20 individuals with RA ranged from 0.53 to 0.96; inter-rater reliability ranged from 0.89 to 1.0. Test–retest reliability in 26 individuals with OA ranged from 0.7 to 0.96; inter-rater reliability ranged from 0.99 to 1.0 [38,39].

The peg-board dexterity test measures the time taken in seconds to place and remove nine pegs into the nine holes. Applied dexterity is the total time taken (seconds) to complete the following tasks: lacing a shoe, tying a bow, fastening/unfastening four buttons, fastening/unfastening two safety pins, cutting putty with a knife and fork, and manipulating coins into a slot.

Applied strength will be measured by the total number of soup cans lifted in a tray and the volume (ml) of water lifted in a pitcher.

Grip strength of the dominant hand will be clinically tested using a handheld dynamometer (Biometrics isometric hand dynamometer G100; Biometrics Ltd, Cwmfelingach, Gwent, UK). Grip strength will be recorded in kilograms and the best score out of the three consecutive trials will be used for analyses. Similarly, three-point pinch strength will be measured using a pinch meter (Biometrics precision pinch meter P200; Biometrics Ltd).

#### Secondary outcome measures

The secondary outcome measures are the DASH questionnaire and an exercise log diary.

The DASH questionnaire, a reliable and valid outcome measure in the arthritis population [40,41], will be used to measure self-reported hand function ability. The DASH has 30 disability/symptoms questions on difficulties in activities of daily living and scores range between 0 and 100. Higher scores indicate severe disability.

A personal exercise log diary will be used to measure exercise compliance. The number of completed exercise sessions out of 24 total exercise sessions in 6 weeks will be calculated. Any adverse symptoms such as an increase in pain or stiffness experienced due to exercising, technical difficulties reported by the participants and the study completion rate will also be documented

A computer-based paddle game with two modes – predictable visual tracking and random play – has been developed to objectively quantify the quality and accuracy of finger hand movements during manipulation of a broad range of common objects independent of physical properties, anatomical requirements and task goal/context [42,43]. For the present study, the tool will be designated as an exploratory outcome measure.

For the predictable visual tracking, predictable, sinusoidal visual tracking (configurable amplitude and frequency) provides a controlled visual input to guide a motor task. An instrumented object will be held by a specific grasp and moved rhythmically in concert with the moving visual target on the computer screen. The position coordinates of the onscreen moving target cursor and the actual object motion will be synchronously logged and saved. The data will be then processed and analyzed using custom analysis routines written in Matlab (The Math Works, Natick, MA, USA).

Quality and accuracy of finger hand movements during tracking will be measured by spatio-temporal accuracy outcomes. Based on the known target trajectory and the user motion, the coefficient of determination will be calculated (Figure 4A). The coefficient of determination determines the overall movement quality of the manipulation task and the values range between 0 and 1. Values near to 1 indicate close fits of the user motion signals with the target cursor motion, and values far from 1 explain the least fit.

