### Home program training sessions

Based on clinical experience and pilot data, three training sessions for approximately 45 to 60 minutes each time are essential before initiating the home program. Each participant from both groups will attend the sessions within 7 to 10 days after the baseline visit.

Care will be taken to ensure that each participant is educated well to perform their respective interventions and to record pain and stiffness levels using computer software. The experimental group will also be shown how to instrument personalized objects with the mouse and how to access the computer games. All participants will be given an opportunity to discuss, clarify and ask questions regarding their home program.

The control group will be provided with medium-resistance therapeutic putty (85 g) and a dumbbell as home program accessories. The experimental group will be provided with an equipment package that includes a motion-sense mouse, a set of personalized objects and commercial computer games, and a few accessories such as Velcro strips and wooden dowel for object instrumentation. Both groups will be provided with software for use on their home computer to record and store pain and stiffness levels using separate 0 to 10 numerical verbal rating scales, before and after each exercise session.

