### Six-week home program

After the training sessions, both groups will be provided with a written protocol of their home program. The protocol will include clear description of each exercise/manipulation to be performed, number of repetitions (control group) or minutes of play (experimental group) and the number of sessions per week.

The control group will perform the conventional hand exercise program, and the experimental group will perform the task-oriented training with personalized objects, selected by the clinical judgment drawn from the baseline findings.

At the start of the home program, the study staff will attend each participant’s home to ensure proper set-up of their respective intervention. A week later, both groups will be contacted through telephone calls or electronic mails to assess their ability to manage the home program. Both groups will be asked to perform their exercises four times per week for 6 weeks. The pain and stiffness files can be saved to a USB flash drive or sent as an email attachment for regular monitoring by the study staff.

Treatment progression or modification will be made for both groups every 2 weeks depending on individual needs and abilities. When no increased symptoms (assuming a benchmark score >5 in the pain and the stiffness scales) are reported during or after exercises, progression will be followed as in Table 1. In cases of any symptoms being reported, the treatment parameters will be modified by reducing the number of repetitions or minutes of play. Any occurrence of increased pain or stiffness continuing over 1 week would be recorded as an adverse event. The intervention will be discontinued and the participant will be referred to his/her general practitioner.

**Table 1 T1:** Treatment progression guidelines for both groups

**Group**	**Progression goals**	**0 to 2 weeks**	**3 to 4 weeks**	**5 to 6 weeks**
Control group	Number of repetitions of each exercise	5	8	12
Experimental group	Personalized objects	3 to 4	4 to 5	5 to 6
Both groups	Strengthening (60 to 70% of one repetition maximum	1 set ×10 repetitions	1 set ×15 repetitions	1 set ×20 repetitions
Both groups	Exercise duration	15 minutes	20 minutes	25 minutes

The study staff providing the interventions will maintain a record of treatment sessions, exercises prescribed and their progression for each participant. Information on adverse symptoms would include severity, duration and the appropriate treatment modifications done.

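### Home symptom ratings exist only for sessions actually done, and two sections use different rules for recording increased pain or stiffness, so safety may be captured unequally if adherence differs by arm

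*Protocol article*

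**What the plan says.** All references are to the Protocol article.

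- **Home ratings (Home program training sessions).** Both groups receive software to rate pain and stiffness "using separate 0 to 10 numerical verbal rating scales, before and after each exercise session". No rating tied to the calendar is described.
- **Adverse symptoms (Secondary outcome measures).** The plan documents "Any adverse symptoms such as an increase in pain or stiffness experienced due to exercising", together with technical difficulties and completion. It does not say who judges the cause.
- **Adverse events (Six-week home program).** "Any occurrence of increased pain or stiffness continuing over 1 week would be recorded as an adverse event". This rule carries no condition on cause.
- **Records (Six-week home program).** "The study staff providing the interventions will maintain a record of treatment sessions, exercises prescribed and their progression for each participant". The next sentence adds: "Information on adverse symptoms would include severity, duration and the appropriate treatment modifications done".
- **Blinding (Randomization).** An independent assessor, blind to allocation, evaluates outcomes at baseline and at the end of week 6. Blinding of participants or treating staff is not described, and participants cannot be blind to the program they perform.
- **Use of the safety data.** The second hypothesis includes treatment safety as part of feasibility, and the abstract's Discussion says the findings will inform decisions on safety.

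**The concern.** The plan's stated capture rules leave two gaps.

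First, the home ratings depend on adherence. A hand too painful to exercise produces no rating on that day, so the rating series can stop when symptoms matter most. If one arm skips more sessions, its symptoms are observed on fewer occasions.

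Second, one rule depends on presumed cause and the other does not. In a chronic painful disease, with disease activity not formally measured (Discussion), it is hard to separate a flare from an exercise effect. Those best placed to make that call, the participant and the treating staff, know the allocation.

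The stake is the safety part of the feasibility conclusion. With about 15 people per arm it will rest on a handful of cases, and observations never collected cannot be recovered at analysis.

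**Working it through.** **1. The plan's own figure.** Four sessions a week × 6 weeks = 24 sessions, which matches the stated total. These are also the only planned home rating occasions, each giving one pre/post pair.

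**2. Home ratings lost when exercise stops.** After stopping at the end of week w, the unrated share is 1 − w/6:

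- week 1: 4 of 24 rated, 83% unrated
- week 2: 8 of 24 rated, 67% unrated
- week 3: 12 of 24 rated, 50% unrated
- week 4: 16 of 24 rated, 33% unrated

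A pause of 8 days, just long enough to pass the one-week threshold, loses 8 × 4/7 = 4.6 expected pairs. At an assumed adherence of 60 to 80%, the loss is 24 × 0.2 = 4.8 to 24 × 0.4 = 9.6 pairs per person. The documents do not show what share of these would be symptomatic days.

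**3. The two recording rules side by side.** Reading the cause condition under Secondary outcome measures as it is worded:

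| Increase in pain or stiffness | Secondary outcome measures | Six-week home program |
|---|---|---|
| 1 week or less, put down to exercise | documented | not an adverse event |
| 1 week or less, put down to the disease | not covered | not an adverse event |
| over 1 week, put down to exercise | documented | adverse event |
| over 1 week, put down to the disease | not covered | adverse event |

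The second row falls outside both rules. In the fourth row the two sections disagree. The over-one-week rule also needs evidence of duration. Home ratings cannot supply it for someone who has paused, so it must come from the participant's report or from staff contact.

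**4. Other symptom data.** The assessment tool rates pain and stiffness at baseline and week 6, and the DASH includes symptom questions. Someone who leaves before week 6 has neither at the end. With only two assessments, last observation carried forward gives that person the baseline DASH score, that is, zero change.

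**5. Illustration of unequal capture.** All rates here are assumptions. The expected recorded count is 15 × true rate × probability of being recorded, with the same true rate in both arms:

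- True rate 20% (3 of 15), recorded 80% vs 50%: 2.4 vs 1.5 (16% vs 10%)
- True rate 20%, recorded 90% vs 30%: 2.7 vs 0.9
- True rate 40% (6 of 15), recorded 80% vs 50%: 4.8 vs 3.0
- True rate 40%, recorded 90% vs 30%: 5.4 vs 1.8

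The artificial gap runs from 0.9 to 3.6 participants. Exchanging the arms reverses its sign.

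**The case against.** The strongest reply is that the plan has several other routes to symptoms. Persistent increases are adverse events whatever their cause. The phrase under Secondary outcome measures follows such as, so it may be only an example, and the two sections may be two tiers: symptoms and events. Missed sessions appear in the diary, completion is documented, participants are contacted after a week, and treatment is reviewed every two weeks. Tick-boxes and form fields are also details that an article may leave to the full protocol.

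Much of this stands, and it rules out three stronger readings that a reader might infer:

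- **That people who stop because of pain will look symptom-free.** This is not supported. Their ratings up to stopping are kept, their missed sessions and non-completion are counted, and an increase lasting over a week is an adverse event. The gap is limited to the unrated period, shorter episodes and those who leave before week 6.
- **That an empty rating file counts as absence of symptoms and so permits progression.** The text does not say this. It refers to symptoms "When no increased symptoms (assuming a benchmark score >5 in the pain and the stiffness scales) are reported during or after exercises" and is silent on missing files.
- **That unblinded attribution drives a between-arm safety comparison.** The Statistical analysis plan section names no such test, and the second hypothesis most naturally attaches the comparison to completion rate. If control did complete less, session-bound ratings would tend to make control look safer, against the experimental program. That a game is blamed less often than an exercise is conjecture.

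The reply does not remove the core. The rating schedule and the cause condition are stated rules, not omitted detail. The diary count shows that a session was missed but not why. The two-tier reading still leaves short increases put down to the disease with no clear home.

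**Conclusion.** The point holds in limited form. Home ratings lapse whenever sessions lapse, and the two sections set different conditions for recording an increase in pain or stiffness. If adherence differs by arm, or people who know the allocation attribute symptoms differently, a side-by-side description of safety can be distorted.

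The loss of home rating occasions follows directly from the schedule: 67% for someone who stops after week 2, for example. The effect on recorded counts is unknown in size and direction. The gaps of 0.9 to 3.6 participants per 15 rest wholly on assumed true rates and recording probabilities. No sample size, power figure or planned test depends on this. It is a worthwhile, inexpensive improvement to data capture and does not threaten the main hand-function comparison.

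**What to change.** - **Home program training sessions:** collect the 0 to 10 pain and stiffness ratings on the four scheduled days each week in both arms, whether or not the session is done, with a reason for each skipped session (symptoms, technical, other).
- **Secondary outcome measures:** drop the cause condition. Record every increase in pain or stiffness, keep presumed cause as a separate descriptive field, and report the all-cause count by arm.
- **Secondary outcome measures and Six-week home program:** reconcile the wording so that both say the same thing about what is recorded as an adverse symptom and what as an adverse event. This concerns recording only and leaves the clinical rules on progression and discontinuation as they are.

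The cost is some wording, an extra field in the diary or software, a few seconds from the participant per skipped session, and a somewhat higher recorded count of adverse symptoms.

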**Figure 4 F4:**
[figure not shown]
**Objective variables of the predictable tracking task.** (**A**) Coefficient of determination of user motion trajectory. Bold lined waveform, user motion signal; thin line, reference waveform for a manipulation task. (**B**) Temporal accuracy. Bold lined waveform in the top plot, reference waveform; light shading, user motion signal for a manipulation task. A maximum and minimum point on the up and down cycles of the user signal is shown. The time taken to reach maximum and minimum points for each movement cycle is compared between the two signals. (**C**) Amplitude consistency. An arbitrary line drawn on a user motion signal represents amplitude consistency in upward and downward directions.

Temporal and amplitude accuracy measures will be determined at the turning points of each cycle of the user motion trajectory (Figure 4B,C). For temporal accuracy, the time taken to reach maximum and minimum points of each cycle of the user motion will be subtracted from the time of the respective target cursor motion maximum and minimum. Average absolute temporal accuracy (in milliseconds) of maxima and minima for all of the cycles will thus be determined. The amplitude consistency of the object motion will be determined by the coefficient of variation of the average movement amplitude in both directions.

For episodic (random) play, the goal of this game mode is to move the paddle (game sprite) to hit the random targets moving vertically top to bottom or horizontally from left to right of the computer screen. The game will be played using an instrumented object that generates a logged game file to record the time index and coordinates of each game target and to record the position coordinates of the game paddle that slaves to player’s movements (representing the respective object manipulation task). The data will then be processed and analyzed in Matlab.

Each one minute of game play can provide around 30 to 40 player movements (multiple events). These movements can be parsed and sorted by movement direction and movement amplitude/speed. Figure 5 shows the parsed movements in a gaming session of 2 minutes. Different features of the player’s movements provide a basis for objective quantification of variables such as: number of hits/misses of the paddle on the random targets; time measured between the appearance of the target to the start of the paddle movement (motor response time); time taken to reach the target location from the paddle initial location (movement execution time); and movement path length from start to end of all gaming events.

**Figure 5 F5:**
[figure not shown]
**Parsed movements from a random game play.** Outcome measures derived from episodic game play are shown.

The tool is also embedded with two separate numerical verbal pain and stiffness scales. The pain scale ranges from 0 (no pain) to 10 (unbearable) and stiffness from 0 (none) to 10 (cannot move). These scales will appear in sequence on the computer monitor before and immediately after each pre-timed sinusoidal tracking or the random game. Participants will be asked to verbally rate their pain and stiffness intensity before and after each manipulation task. The study staff record them, and they will be automatically saved along with the user motion data.

The tool will be used to evaluate quality and spatio-temporal accuracy during four manipulation tasks with objects such as a salad tongs, a small bead, jug and a turning knob. These objects are selected to represent a diverse range of manipulation tasks needing different functional requirements of handling. Note: in order that there is no practice effect, these four objects will not be included for the experimental group. Our previous pilot work has reported that the jug and salad tongs were difficult to manipulate in people with RA or OA. So these two manipulation tasks will be evaluated in predictable tracking mode with a duration of 30 seconds. Skill and efficiency of the other two manipulations will be evaluated while playing the random game for 90 seconds. Evaluation of all four tasks may take approximately 7 to 10 minutes.

The measures derived from both game modes of the computer-based hand assessment tool are as follows: predictable tracking – task performance (coefficient of determination), spatio-temporal accuracy measures (temporal accuracy, amplitude consistency), pain and stiffness intensity; and episodic (random) game – success rate (number of target hits), movement skill (average motor initiation time, average motor response time), movement efficiency (movement path length), and pain and stiffness intensity.

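### Withholding the four test objects controls object-specific practice only; the experimental arm still practises the type of cursor control that the exploratory tool scores

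*Protocol article*

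**What the plan says.** The passages are all in the protocol article.

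- **Secondary outcome measures, text after Figure 5.** Four objects (salad tongs, small bead, jug, turning knob) are used for testing. The note on them reads: "in order that there is no practice effect, these four objects will not be included for the experimental group".
- **Secondary outcome measures, the two game modes.** In tracking mode an instrumented object follows a moving on-screen target. In random play it moves a paddle towards targets: "The game will be played using an instrumented object that generates a logged game file". The movement measures are tracking fit, temporal accuracy, amplitude consistency, target hits, response time and path length. The tool is labelled exploratory.
- **Interventions, Experimental group.** "The random manipulative movements described for each object task will be used to control the motion of the computer game cursor".
- **Home program training sessions, experimental arm.** "The experimental group will also be shown how to instrument personalized objects with the mouse and how to access the computer games". On equipment: "The experimental group will be provided with an equipment package that includes a motion-sense mouse", together with "a set of personalized objects and commercial computer games".
- **Home program training sessions, control arm.** "The control group will be provided with medium-resistance therapeutic putty (85 g) and a dumbbell as home program accessories". The software that control receives has a different purpose: "Both groups will be provided with software for use on their home computer to record and store pain and stiffness levels".
- **Baseline visit, Randomization and the final session.** Outcomes are assessed at baseline and at the end of week 6, with no distinction between arms.

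**The concern.** The note treats practice as belonging to the object. A score for hitting moving targets or tracking a sine wave depends on two things: how well the hand manipulates the object, and how well the person has learned to turn object movement into cursor movement. Withholding objects acts on the first only. The second is rehearsed throughout the home programme in one arm and not in the other.

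The absence of a practice effect is stated as a property of the measure. A reader who relies on it could take a better week-6 tool score in the experimental arm as evidence of transfer to hand function, when some or all of it could be familiarity with the mode of control. The problem would remain even if no object used in testing were ever used in training.

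**Working it through.** The protocol gives no effect size, standard deviation or power for the tool, so there is no stated figure to reproduce. The check has three steps.

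**1. Training and testing side by side.**

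| | Experimental training | Control training | Exploratory tool |
|---|---|---|---|
| Action | Manipulate an instrumented object | Hand exercises, putty, dumbbell | Manipulate an instrumented object |
| What it drives | Game cursor | Nothing on screen | Tracking cursor or game paddle |
| Software | Commercial games | Pain and stiffness recording | Purpose-built paddle game |

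The experimental arm and the tool share the type of control, not the game. Control training shares neither.

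**2. Scheduled exposure.** Inputs: four sessions a week for 6 weeks (Six-week home program); 15, 20 and 25 minutes per session in three two-week blocks (Table 1); two tracking tasks of 30 seconds and two random games of 90 seconds (text after Figure 5).

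- Sessions: 4 × 6 = 24, which agrees with the total given for the exercise diary.
- Sessions per block: 4 × 2 = 8.
- Home minutes: 8×15 + 8×20 + 8×25 = 120 + 160 + 200 = 480.
- Scored tool time per assessment: 2×30 s + 2×90 s = 240 s = 4 minutes, within the stated 7 to 10 minutes overall.

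Before the week-6 test, control has therefore had about 4 minutes of scored tool play, at baseline. The experimental arm has had the same 4 minutes plus up to 480 scheduled home minutes. That figure is a maximum: it assumes every session is completed, and the duration row is not stated to be game play throughout, since strengthening is prescribed in sets and repetitions. The three supervised sessions (3×45 to 3×60 = 135 to 180 minutes) are left out because they also cover instruction and questions.

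**3. What an interface-only difference could do (illustration).** Suppose hand function does not differ between arms, interface familiarity shifts the experimental arm's tool score by d standard deviations, and the scores are compared by an unpaired t test. With 30 participants at 1:1, n = 15 per arm, df = 28, two-sided alpha 0.05 and noncentrality d × √(15/2), the chance of a significant result is:

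| Assumed d | Chance of P < 0.05 |
|---|---|
| 0 | 5.0% |
| 0.2 | 8.3% |
| 0.3 | 12.5% |
| 0.5 | 26.2% |
| 0.8 | 56.2% |
| 1.0 | 75.3% |

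Every d is an assumption. The article gives no value, and its statistical analysis section does not list the tool among the outcomes to be tested. The table shows only that a moderate familiarity effect would matter if the tool were tested this way.

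**The case against.** The case on the other side has real force.

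- **The tool is exploratory.** It is labelled so, and its measures are not in the outcome list of the statistical analysis plan section. The article uses the term performance-based for the Arthritis Hand Function Test and gives self-reported function to the DASH; neither is scored through a game. This stands and limits the consequence. A reader might infer that the main test of the first hypothesis is compromised; the document does not support that.
- **Testing on untrained objects is a sensible generalisation check.** The programme aims at acquiring manipulation skill, so a better score on a new object may be the intended transfer. This stands too. A reader might infer that any tool difference must be pure device learning, or that the direction of bias is certain. Neither is shown; the two explanations cannot be separated, and learning would be expected, not proved, to favour the experimental arm.
- **Control does use the tool.** It is assessed at baseline and week 6, so it would be wrong to say that control never meets the interface. Nor is the interface shown to be identical: the games differ, and the article does not say outright that the tool uses the same mouse, although Figure 1 shows a turning knob fitted with it.
- **Minutes of practice are not bias.** A reader might divide 480 by 4 and speak of at least 120 times the test length. But 480 is a full-adherence ceiling, not a floor, and the ratio measures exposure only.
- **All participants own and can use a computer.** This narrows differences in general computer skill but does not equalise practice in steering with an instrumented object.

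None of these rescues the statement that no practice effect exists.

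**Conclusion.** The point holds in a limited form. Withholding the four objects limits object-specific practice; it does not remove practice in instrumented-object cursor control, which the experimental arm trains for up to 480 scheduled home minutes and control does not train at all. Between-arm differences in the tool's movement measures are therefore confounded with interface familiarity. The size of that confounding cannot be derived from the document.

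The conclusion rests on two readings: that the skill of steering with an instrumented object carries over from commercial games to the paddle game, and that control has no access to such steering outside the assessments, as its listed equipment implies. It does not touch the Arthritis Hand Function Test, the DASH, or the 0 to 10 pain and stiffness ratings, which are verbal ratings and not cursor scores.

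The jug raises a separate matter: it is among the withheld test objects and also appears as object 6 of the experimental programme. Those passages need reconciling, but doing so would leave the present point unchanged.

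**What to change.** 1. Replace the statement about practice with one saying that withholding the four objects limits object-specific practice only, and that between-arm differences in tracking fit, temporal accuracy, amplitude consistency, hits, response time and path length are confounded with interface familiarity.
2. State that such differences will not, on their own, be read as better hand function, and that the hand-function part of the first hypothesis rests on the Arthritis Hand Function Test and the DASH. Confine this to hand function: the same hypothesis also names pain and stiffness, whose ratings should stay as planned.
3. Optionally, give both arms the same short unscored familiarisation run before the scored runs at each assessment. This reduces novelty but cannot offset six weeks of unequal practice, so it supplements the wording and does not replace it.

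The cost is a few sentences, a few extra minutes per assessment visit if the third step is adopted, and a weaker claim from an exploratory measure.
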